## Abstract

**Background:**

Caring for a person with borderline personality disorder is associated with poor outcomes including elevated psychological distress and burden. This study will compare the effectiveness of two brief psychoeducational programs for carers of youth presenting for early intervention for borderline personality disorder features. The protocol for this study is presented here.

**Methods:**

The study is a single-centre parallel group, randomised controlled trial. As a family unit, relatives, partners and friends (‘carers’) are randomly allocated to one of two treatment arms to receive either an online borderline personality disorder psychoeducation program, or both the online psychoeducation group and a face-to-face group program, *Making Sense of Borderline Personality Disorder*. Carers are assessed at baseline and follow-up (4 weeks after the intervention). It is expected that participants who received the combined group and online programs will have better outcomes than those who received the online program alone. The primary outcome is carer burden, assessed using the negative appraisal subscales of the Experience of Caregiving Inventory. Secondary outcomes include positive experiences of caregiving, coping, self-rated personality disorder knowledge, psychological distress, expressed emotion and quality of life.

**Discussion:**

This will be the first published evaluation of a psychoeducational intervention for carers of youth with borderline personality disorder features using a randomised controlled trial design. The results have the potential to inform clinicians and carers about the effectiveness of brief interventions designed to support families and friends of young people with borderline personality disorder, and what medium those interventions should utilise.

**Trial registration:**

Prospectively registered with the Australian New Zealand Clinical Trial Registry ACTRN12616000304437 on 08 March 2016.

## Background

Borderline personality disorder (BPD) is a common and severe mental disorder comprising difficulties with affect regulation, impulsivity, interpersonal relationships and identity [1]. BPD usually has its onset during adolescence and early adulthood [2] and has been shown to be a reliable and valid diagnosis during these developmental periods [1, 3]. Families and friends (henceforth “carers”) of individuals with BPD experience high rates of psychological symptoms, including anxiety and depression [4, 5], objective and subjective burden, and grief [6, 7]. These rates are higher than the general population [4] and greater than carers of individuals with other severe mental illnesses [6, 7]. Such rates might arise from the experience of caring for a loved one with BPD and/or from difficulties (e.g., psychopathology) that might cluster within families of those with BPD.

Carers want information about BPD [8–10]. However, few psychoeducational interventions have been developed and, to the authors’ knowledge, just three of these programs have been subjected to formal empirical evaluation: ‘Dialectical Behaviour Therapy - Family Skills Training’ (DBT-FST; [11, 12]); ‘Family Connections’ [13] and ‘Staying Connected when Emotions Run High’ [14]. These evaluations indicate that psychoeducational programs consistently reduce carer burden and grief and increase perceived capacity to cope [13–15], but their effects upon psychological distress have been mixed [15, 16].

The above programs were primarily designed for carers of adults, although DBT-FST has been applied to a younger age group (13 to 18 years, [16]). Our team has developed and empirically tested the first psychoeducational group program designed specifically for carers of youth with BPD features. The *Making Sense of BPD* program (MS-BPD; [17]) accommodates the needs of carers of those with early-stage disorder and places BPD in an appropriate developmental context. In a pre-post, repeated measures design pilot study, MS-BPD was associated with reduced subjective burden (i.e., feelings and attitudes, such as shame) and increased personality disorder knowledge, but not with changes in objective burden (e.g., financial problems) or distress [17]. Several methodological issues limit the generalisability of these findings. The absence of a comparison group meant that changes could not solely be attributed to MS-BPD. Most participants completed the post-intervention measures on the day of the final MS-BPD session (day 15) and it is unclear what effect the program might have had on outcomes with longer follow-up. It was assumed that each round of the group was the same, not accounting for potential group clustering effects. Further, the study relied on a self-report screening measure for BPD, rather than a diagnostic assessment, and had a modest sample size of 23 carers. The pilot study’s promising findings warrant testing with a larger randomised controlled trial (RCT) that addresses these limitations. This paper describes the protocol for such an RCT.

This RCT aims to evaluate the effectiveness of an online BPD psychoeducation program (Online), compared with the online program delivered in conjunction with MS-BPD (Online+MS-BPD) for carers of youth with BPD. The trial’s hypotheses are that at the primary end-point of week seven, participants receiving Online+MS-BPD will have superior results on the primary (carer burden) and secondary (positive experience of caregiving, coping, personality disorder knowledge, distress, expressed emotion and quality of life) outcome measures, compared with participants receiving Online.

## Methods

### Study design

The study is a single-centre parallel group, single-blinded RCT. The study was developed in accordance with Good Clinical Practice (GCP) Guidelines and Standard Protocol Items; Recommendations for Interventional Trials (SPIRIT; [18]). The trial is being conducted by Orygen, The National Centre of Excellence in Youth Mental Health (Orygen). It was approved by the Melbourne Health Human Research Ethics Committee (HREC2014.105) and conducted in accordance with the Declaration of Helsinki. The trial was funded by a Melbourne Health Grant In Aid (GIA-013-2015) and was prospectively registered (ACTRN12616000304437). Members of Orygen’s Sponsor Operations Department monitors the trial.

### Study setting

The study is being conducted at the Helping Young People Early (HYPE) program at Orygen Youth Health (OYH) [19], a publically-funded youth mental health service in Melbourne, Australia. HYPE provides specialist early intervention for youth with severe personality disorder, offering clinical case management, individual cognitive analytic therapy (CAT) and general psychiatric care [19]. HYPE offers indicated prevention [20] and early intervention to young people with three or more DSM-5 BPD criteria, as there is evidence that ‘sub-threshold’ features of BPD are clinically significant [21]. There are no specific exclusions for HYPE, apart from meeting criteria for entry into Orygen’s first-episode psychosis program. The trial interventions are additional components of the care offered by the HYPE program to OYH clients with BPD features.

### Inclusion and exclusion criteria

Study participants are: (i) relatives, partners, or friends of a HYPE client; (ii) able to give informed consent; (iii) sufficiently fluent in English; and (iv) able to comply with study procedures. Carers are excluded if their client meets the trial’s exclusion criteria or if they have previously participated in MS-BPD or Online. Carers may not have a professional relationship with a client, for example, child protection workers or staff at residential care units are not eligible. The clients must be: (i) attending HYPE; (ii) aged 15 to 25 years (inclusive); (iii) able to give informed consent; (iv) sufficiently fluent in English; and (v) able to comply with study procedures. Clients are excluded if they are eligible for OYH’s first-episode psychosis program [22, 23].

### Discontinuation and withdrawal

Carers are discontinued or withdrawn if their participation interferes with appropriate clinical management of the client’s risk to self or others, consent is revoked, or an event (e.g. inappropriate behaviour in the MS-BPD group setting) leads to discontinuation at the discretion of the investigators. These participants remain in the sample to be analysed.

### Interventions

*MS-BPD* is a manualised group program designed for carers of young people with BPD features, informed by the principles of CAT. It consists of three two-hour sessions facilitated by two specialist youth mental health clinicians; the third session is co-facilitated by a family peer support worker, with lived experience of caring for a mentally-ill young person. MS-BPD is run in the evening over three consecutive weeks (i.e., on days one, eight and fifteen). It aims to provide an explanatory model of the causes of BPD, psychoeducation about the rationale for and nature of BPD treatment, along with information about common difficult relationship processes and possible ways to resolve these. The group is interactive, and participants are encouraged to ask questions and to share their experiences. Treatment completion is defined as attending two or more sessions.

The *Online* program was also developed specifically for carers of youth with BPD features. It comprises two modules: ‘Introduction to Early Intervention for Borderline Personality Disorder’ and ‘Caring For A Young Person with Borderline Personality Disorder - Information for Families and Friends’. The modules take approximately 30 and 20 min to complete, respectively, and include written material and video interviews with experienced clinicians, clients and parents. The program is self-directed, can be accessed multiple times, and is accessible at all times. Date, time and duration of each visit is recorded and treatment completion is defined as using the program for at least 80% of the mean time it takes to complete the entire program.

### Treatment integrity

MS-BPD integrity is maintained through regular facilitator supervision and use of the MS-BPD manual and standardised program resources (e.g., presentation slides). The fixed design of the Online program ensures its integrity.

### Outcome measures

The primary outcome is burden, defined as the combined total score of negative appraisal subscales of the Experiences of Caregiving Inventory (ECI; [24]). The secondary outcomes include positive experience of caregiving (ECI total positive appraisal subscale; [24]), coping (Coping Inventory for Stressful Situations; [25]), self-rated personality disorder knowledge (selected items from Personality Disorder Knowledge, Attitudes and Skills Questionnaire, modified for use with carers; [26]), distress (Kessler Psychological Distress Scale; [27]), expressed emotion (Family Questionnaire; [28]), and quality of life (Assessment of Quality of Life - 8 Dimensions and Quality of Life Enjoyment and Satisfaction Questionnaire - Short Form; [29, 30]). Subsidiary measures capture demographic, treatment/resource use and diagnostic information (e.g. Structured Clinical Interview for Diagnostic and Statistical Manual of Mental Disorders, Fourth Edition, Axis I and II disorders; [31, 32]). Table 1 lists the trial measures.

**Table 1 Tab1:** Schedule of outcome measures

	Time point	
Measure	Baseline	Week Seven
*Primary Outcomes*		
Combined total negative appraisal subscales of the Experience of Caregiving Inventory (ECI)	✔	✔
*Secondary Outcomes*		
Combined total positive appraisal subscales of the ECI	✔	✔
Coping Inventory for Stressful Situations (CISS)	✔	✔
Personality Disorder Knowledge Attitudes and Skills Questionnaire (PDKASQ) ^a^	✔	✔
Kessler Psychological Distress Scale (K-10)	✔	✔
Family Questionnaire (FQ)	✔	✔
Assessment of Quality of Life (AQoL-8D)	✔	✔
Quality of Life Enjoyment and Satisfaction Questionnaire – Short Form (Q-LES-Q-SF)	✔	✔
*Subsidiary Measures*		
Demographics - carers	✔	✔
Carer-specific Resource Use	✔	✔
Demographics – clients ^b^	✔	
Treatment Data ^b^		✔
SCID-II Personality Questionnaire for BPD ^b^	✔	
Diagnosis DSM-IV SCID-I/P ^b^	✔	
BPD diagnosis DSM-IV SCID-II ^b^	✔	

aThree items, modified for use with carers rather than clinicians

b Measures completed with clients, not carers

*BPD* borderline personality disorder, *DSM-IV* Diagnostic and Statistical Manual, Fourth Edition, *SCID* Structured Clinical Interview for DSM-IV; SCID-I/P=SCID Axis I Disorders, Patient Version; SCID-II=SCID Axis II Disorders

### Procedure

Participants (and a parent/legal guardian for minors) are asked to provide written informed consent. A carer’s participation is not dependent on their young person also consenting to participate. Carers who decline participation in the trial may still utilise the interventions. The interventions are delivered in rounds, approximately every 12 weeks. Information collected as part of routine clinical care [33] is extracted from consenting clients’ medical records. Carers are given baseline questionnaires up to 2 weeks prior to the forthcoming round, and upon completion of these, carers are randomly and consecutively assigned to the next Online or Online+MS-BPD as a family unit. Follow-up questionnaires are issued at week seven, (4 weeks after the intervention), and carers have up to 4 weeks to complete these. The baseline and follow-up questionnaires are self-rated, online or in hard copy. Figure 1 shows the participant flow chart.

**Fig. 1 Fig1:**
[figure not shown]
CONSORT flow diagram for MS-BPD trial

### Randomisation and blinding

Randomisation occurs in a 1:1 ratio using a password-protected computer program with a sequence that was computer-generated by an independent statistician. Treatment allocation uses randomised permuted blocking, stratified by client’s sex and age (< 18 years old; 18 years is the mean age of HYPE clients). The trial statistician is blinded to group allocation, but due to the nature of the interventions and outcome measures (i.e., self-rated questionnaires), the participants, clinicians and researchers are not blinded.

### Data integrity

Most data are entered directly online by the participants. For data collected in hard copy, data entry verification will be undertaken on a random selection of 20 % of cases at each time point, with an a priori acceptable error rate of 0.5%.

### Statistical analysis

The analysis will be by intention-to-treat. Two sources of potential non-independence (clustering) of observations are: (1) participation in the intervention by more than one carer associated with an individual client (a ‘unit’); (2) the round of MS-BPD attended. Thus, the unit is considered a cluster and within the Online+MS-BPD arm, the MS-BPD round attended is considered the intervention cluster (IC). Such a design is referred to as a partially nested, clustered RCT [34]. To accommodate this design, mixed models will be used with unit and IC fitted as random factors [34]. Although low levels of missing data are expected, mixed models have the advantage of retaining the observations of participants who have missing data [35]. The models will be extended to include baseline and time varying covariates as well as categorical variables that might confound outcomes and require adjustment. A two-step approach will first identify individually significant and near-significant associations with outcome measures, and then simultaneously fit these variables in a multiple predictor model. This approach will be applied to each of the outcomes specified in the hypotheses. Adaptations of this approach will be used to explore predictors of the outcomes. Further, given that mothers have been the most frequent attendees of MS-BPD to date, exploratory analyses of this subgroup alone will occur. It is recognised that these analyses will have reduced power to detect change and the study has not been powered for subgroup analyses.

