While this trial’s design attempted to overcome problems identified in previous studies, there are some anticipated limitations. This trial will not assess the maintenance of any changes over the medium- to long-term. Future studies would be strengthened by having additional follow-up assessments, longer than four to eight weeks post-intervention. Compared with participants in the Online arm, participants in the Online+MS-BPD arm might have greater exposure to psychoeducation, given that they will have the Online material repeated by MS-BPD facilitators. The trial results will therefore need to be interpreted with this in mind, with the Online usage data and MS-BPD attendance rates elucidating whether the ‘dose’ of psychoeducation differed between the trial’s arms. Further, reflective of ‘real-world’ clinical practice, carers are free to access additional carer-specific resources, which might confound the trial’s findings. OYH, for example, offers individual sessions with specialist family clinicians and peer support from trained family peer support workers. However, data on the use of such resources is being collected and will be controlled for in our analyses. Although beyond the scope of this trial, if the online program and MS-BPD prove to be effective for carers, an examination of whether improved carer outcomes might be associated with better outcomes for young people with BPD is warranted. To the authors’ knowledge, this relationship has not previously been empirically tested and will be an important extension of the field.

Notwithstanding these limitations, the trial design has several strengths. The trial benefits from broad inclusion criteria, with few exclusion criteria, which enables the recruitment of a sample that reflects the clients and carers who present to government-funded specialist mental health services in Melbourne, Australia. Carers representing a range of different types of relationships are included, rather than limiting the study to just parents, or mothers, as is commonly the case [7]. While much of the research to date has focused on those caring for females with BPD, this trial includes carers of both males and females with BPD [7]. BPD is assessed with a standardised clinical interview. Lastly, the manualised nature of MS-BPD and the pre-programmed MS-BPD and Online resources ensure treatment integrity.

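### Covariates for the primary outcome are chosen by significance screening on the outcome data, and no fixed model is named as primary

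*Protocol article*

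**What the plan says.** The Statistical analysis section starts from an intention-to-treat mixed model with family unit and MS-BPD round (the intervention cluster, IC) as random factors. It then adds: "The models will be extended to include baseline and time varying covariates as well as categorical variables that might confound outcomes". The selection rule follows: "A two-step approach will first identify individually significant and near-significant associations with outcome measures", "and then simultaneously fit these variables in a multiple predictor model". Its scope is explicit: "This approach will be applied to each of the outcomes specified in the hypotheses". The hypotheses at the end of the Background include the primary outcome: "participants receiving Online+MS-BPD will have superior results on the primary (carer burden) and secondary".

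Three other places bear on the rule:

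- The Discussion says of additional carer support that "data on the use of such resources is being collected and will be controlled for in our analyses". Table 1 shows carer resource use recorded at baseline and at week seven.
- The Procedure section says a carer's "participation is not dependent on their young person also consenting to participate". Clinical information from clients' "medical records" is extracted for consenting clients only.
- Sample size determination assumes a correlation of 0.5 between baseline and outcome.

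**The concern.** Randomisation already protects the comparison from systematic confounding. Adjustment in the main analysis serves to gain precision and to respect the stratified design, and neither aim requires the outcome data to pick the covariates. Under the stated rule the model for carer burden is known only once carer burden has been observed. There is no cut-off for near-significance and no covariate that must be kept, so several models are consistent with the text, and each outcome may end with a different one.

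The candidates are also not confined to baseline. The trial has only two assessments, so a time-varying covariate necessarily contributes a week-seven value, taken after randomisation. Use of other carer support may itself depend on whether a carer was offered the group. Adjusting for it can move the estimate away from the total effect of allocation, which is what the hypotheses and the intention-to-treat statement concern.

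**Working it through.** **1. Is the primary outcome covered?** The rule applies to all outcomes in the hypotheses, and carer burden is the first of them. No sentence names the unextended mixed model as primary. The data-driven rule is stated, not left open, so a later analysis plan that fixed the covariates would have to depart from the article.

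**2. Do the passages agree on resource use?** Under the two-step rule a variable enters only if it screens in. The Discussion promises adjustment for resource use without that condition. The two do not match, and both allow a post-randomisation variable into the model.

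**3. Is the baseline score secured?** With r = 0.5, baseline adjustment multiplies residual variance by 1 - 0.5² = 0.75. Without it, the required sample is 1/0.75 = 1.33 times as large. The analysis text does not force the score in.

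**4. Does screening damage the test?** Simulation with 81 independent carers (54 units × 1.5), ordinary least squares, clustering ignored. Assumed: 8 or 15 candidates besides baseline, and entry at p < 0.10 or p < 0.20. Runs: 4,000 under the null and 2,000 at 0.5 SD.

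| | Fixed baseline-adjusted model | Screened model |
|---|---|---|
| Type I error | 0.046-0.055 | 0.046-0.053 |
| Power at 0.5 SD | 0.71-0.72 | 0.68-0.71 |

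The two treatment estimates differed by an SD of about 0.06 to 0.07 outcome SD. If either model could be reported, type I error was 0.058-0.070. A second simulation (effective n 66, 10 to 30 pure-noise candidates, the same two thresholds) gave 0.048-0.054 for the screened model.

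**5. Conditional loss of carers.** The starting point is the plan's 54 units for 80% power at 0.5 SD. Total carers = 4 × ((z_α + 0.8416)/0.5)² × 0.75 × design effect, divided by 1.5 to give units. The article states no alpha; 5% is assumed.

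- Two-sided 5%, design effect 1.24: 4 × (2.8016/0.5)² × 0.75 × 1.24 = 116.8 carers, or 77.9 units.
- One-sided 5%, design effect 1 + (1.5 - 1) × 0.2 = 1.1: 4 × (2.4865/0.5)² × 0.75 × 1.1 = 81.6 carers, or 54.4 units.

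Only the second variant returns 54, so both are carried forward. That discrepancy is a separate matter.

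Power = Φ(0.5/SE - z_α), with SE = √(0.75 × design effect) × √(2/n) and n carers per arm:

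| Units lacking the covariate (assumed) | Carers left | Two-sided 5%, design effect 1.24 | One-sided 5%, design effect 1.1 |
|---|---|---|---|
| 0% | 81 | Φ(2.33 - 1.96) = 64.5% | Φ(2.48 - 1.645) = 79.7% |
| 20% | 64.8 | Φ(2.09 - 1.96) = 55.0% | Φ(2.22 - 1.645) = 71.6% |
| 40% | 48.6 | Φ(1.81 - 1.96) = 43.9% | Φ(1.92 - 1.645) = 60.8% |

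**The case against.** The section does set out a simple mixed model before saying that it will be extended, and a reader could take the simple model as primary and the screened one as supporting. The text does not say so. Which model is primary is undetermined, and that is itself the defect; the article does not state that the screened model is the primary one.

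Three stronger readings are tempting and are not supported.

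- *Screening makes the test invalid.* Selection is ignored in the standard errors, but both simulations put type I error near 5%. The modest rise to 0.058-0.070 needs freedom to choose between models.
- *The analyst can steer the result.* Under Randomisation and blinding, the trial statistician is blinded to allocation. This limits steering, although it does not fix the model.
- *Carers will be dropped, against intention-to-treat.* The article names no client-level variable as a candidate. Loss requires that one is offered, that it screens in, and that its missing values are not imputed or otherwise handled. The article's remark that mixed models retain participants with missing data holds for missing outcomes, not automatically for missing covariates. Handling of missing covariates may well sit in an analysis plan that is not shown. Client sex and age are needed for stratification, so the exposure is mainly to diagnosis and treatment data. No non-consent rate is given.

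On the baseline score, the practical risk is small if r really is 0.5: it passed the screen in at least 99.8% of simulated runs. The gap matters more for outcomes with a weaker correlation. The article might also intend baseline as a repeated response in the mixed model, but it does not say this.

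**Conclusion.** The point holds in a limited form. The article applies an outcome-driven covariate rule to all hypothesis outcomes, including primary carer burden, without a forced-in covariate or a named primary model. The main consequences are an estimate not fixed in advance, adjustment sets that can differ by outcome, and possible adjustment for post-randomisation variables. The last can change the effect being estimated; its size and direction cannot be derived from the documents. The shift from screening alone is small beside the 0.5 SD target, under a simulation with assumed candidates and thresholds and no clustering.

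The loss of carers is secondary and conditional, and its power figures rest on an assumed 20-40% non-consent rate and an assumed alpha. The plan should be changed because the remedy is nearly free, not because the test as written is shown to be invalid.

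**What to change.** For every hypothesis outcome, name as primary the mixed model with random effects for unit and for IC (within the Online+MS-BPD arm), adjusted only for that outcome's baseline score, client sex and client age group (under 18, 18 or over). All three should be available for each randomised carer: baseline questionnaires are completed before allocation, and sex and age are stratification factors.

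Keep the two-step screen for the exploratory work on predictors of outcome, which the section already mentions separately, or for a labelled sensitivity analysis. Move any adjustment for post-randomisation resource use there too, and amend the Discussion sentence to match.

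The cost is analysis wording. A strong predictor not foreseen would appear only in a sensitivity analysis.
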